### 2.19. Monitoring

The trial will be monitored regularly by the survey teams and the local trustee, using a specific checklist. Online data access will be restricted to trained staff with unique password-protected accounts. Adverse events associated with the three months smart personalized nutrition intervention will be collected, discussed, and solved among field staff and the local responsible person for the different surveys.

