Level 1 (entry-level) intervention will consist in the use of i-Diet Stance4Health and the analysis of GM and metabolites. Level 2 (advanced level) will consist of the use of i-Diet Stance4Health and the analysis of GM and metabolites (as in the entry level), plus the use of a wearable wrist band only in adults, a metabolomics test to check the presence of metabolism disorders [18,19], and the intake of tannins extracts in pills for adults and in biscuits for children (treated group) or placebo (control group). The wearable band will be used to record physical activity, heart rate, blood pressure, and body composition as well as to refine food intake. Tannin extracts will be produced and distributed looking for a deeper modulation of the GM [16]. All data recorded in i-Diet Stance4Health and by the wearable band and results of the analyses will be recorded in specific databases. In detail, 200 Spanish and German adults will follow the entry-level intervention, and 200 will follow the advanced level intervention, equally divided into control and treated groups. The same criteria will be used for 400 Greek children (100 normal weight, 100 with obesity, 100 with gluten-related disorders, and 100 with allergy/intolerance to cow’s milk). Among them, half will be included in Level 1 and half in the Level 2 intervention.

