### 2.8. Blinding

Blinding of participants will be possible thanks to the use of a placebo instead of tannin pills and biscuits enriched in tannins. Blinding of trial personnel is not possible because of differences between the intervention levels.

Trial personnel who will enroll participants, data collectors, outcome assessors, and data analysts will be blinded to treatment allocation, and an employee outside of the research team will manage data in the computer on separate datasheets.

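### Section 2.19 appears to make association with the intervention a condition for recording an adverse event, so events put down to background disease may be lost and absolute risks understated

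*Protocol article*

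**What the plan says.** Section 2.19 (Monitoring) gives the only rule on adverse events: "Adverse events associated with the three months smart personalized nutrition intervention will be collected, discussed, and solved among field staff". The sentence goes on to name a second party: "discussed, and solved among field staff and the local responsible person for the different surveys". It does not define association, either by cause or by time, and it does not say who decides it.

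Section 2.3 describes the Level 2 product: "the intake of tannins extracts in pills for adults and in biscuits for children (treated group) or placebo (control group". Level 1 has no such product. The children include groups with gluten-related disorders and with allergy or intolerance to cow's milk (section 2.2).

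Section 2.8 makes three statements on blinding:
- Participants: "Blinding of participants will be possible thanks to the use of a placebo instead of tannin pills and biscuits enriched in tannins".
- Staff, first statement: "Blinding of trial personnel is not possible because of differences between the intervention levels".
- Staff, second statement, which also covers those enrolling participants: "data collectors, outcome assessors, and data analysts will be blinded to treatment allocation".

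**The concern.** The qualifier in section 2.19 attaches to the events that are collected, so someone has to link an event to the intervention before it is written down. That is fragile in this population. Section 2.2 excludes children with gluten-related disorders who have no symptoms, so on its wording those enrolled are symptomatic. The milk group includes lactose intolerance, defined partly by symptoms, and IgE-mediated milk allergy. A new gastrointestinal or allergic complaint in such a child is easily explained by the known condition and then leaves no trace.

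Two things are at stake. The first is the absolute frequency of events in children and adults taking tannin extracts or placebo for 12 weeks. The second is comparability. Level 2 participants have a pill or biscuit to blame and Level 1 participants do not, so staff who know the level may link events more readily in Level 2. An event recorded with a doubtful cause can be reclassified later. An event that was never recorded cannot be recovered.

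**Working it through.** The article gives no adverse-event rate, margin or target difference, so there is no stated figure to reproduce. The check has two parts.

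**1. The blinding sentences side by side**

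- The first staff sentence in 2.8 says trial personnel cannot be blinded. The reason it gives is the difference between levels, not between treated and control.
- The second says data collectors, outcome assessors and others are blinded to treatment allocation.
- They are compatible if staff know the level but not the arm within it. The article does not say this, and it does not say which description covers the field staff of 2.19.

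So it is open whether those who attribute events know treated/control status. Knowledge of the level is, on the article's own account, unavoidable.

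**2. What a filter on association does**

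Group sizes come from section 2.3.
- Adults: "200 will follow the advanced level intervention, equally divided into control and treated groups", so 200 / 2 = 100 treated and 100 control in Level 2.
- Children: of 400, "half will be included in Level 1 and half in the Level 2 intervention", so 400 / 2 = 200 in Level 2, and with the same division 100 treated and 100 control.

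Let pT and pC be the true risks and sT and sC the shares of events recorded. Then:
- recorded risks are sT × pT and sC × pC;
- recorded risk ratio = (sT / sC) × (pT / pC);
- if sT = sC = s, the recorded risk difference = s × (pT − pC) and the risk ratio is unchanged.

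All risks and shares below are assumed. Each share is taken to apply to every type of event.

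| True risks (treated, control) | Shares recorded | Recorded risks | Risk difference | Risk ratio |
|---|---|---|---|---|
| 20%, 10% | 100%, 100% | 20%, 10% | 10 points | 2.0 |
| 20%, 10% | 50%, 50% | 10%, 5% | 5 points | 2.0 |
| 20%, 20% | 50%, 50% | 10%, 10% | 0 | 1.0 |
| 20%, 20% | 60%, 40% | 12%, 8% | 4 points | 1.5 |
| 20%, 20% | 80%, 40% | 16%, 8% | 8 points | 2.0 |
| 20%, 20% | 40%, 60% | 8%, 12% | −4 points | 0.67 |

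Rows 2 and 3 are what attribution blind to arm would give: no false difference and an intact ratio, but half the events and half the risk difference gone. At 100 per arm (two-sided 5%, normal approximation for two proportions), power to detect the difference falls from 51% in row 1 to 27% in row 2.

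Rows 4 to 6 need capture to differ between the groups compared. For treated versus control, that requires knowledge of the arm. For Level 1 versus Level 2, knowledge of the level is enough. With a true risk of 20% in both levels and 60% recorded in Level 2 against 40% in Level 1, the records would show 12% against 8%.

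**The case against.** A reader might infer that the plan cannot give an unbiased treated-versus-control comparison of tolerability. The document does not support that. Participants are blinded by placebo, 2.8 says data collectors and outcome assessors are blinded to allocation, and knowing that someone is in Level 2 does not reveal the arm. Equal filtering leaves the risk ratio intact. Nor is such a comparison planned: tolerability is not an outcome in 2.5, and 2.18 contains no safety contrast. The arms also differ in whether diet advice uses gut microbiota composition (2.3), so even complete recording would not isolate the tannin products.

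A reader might also infer that field staff alone judge causality. Section 2.19 says that field staff and a local responsible person discuss and solve events. It assigns the causality judgement to nobody. The restriction itself is a reading of the sentence: the word *only* does not appear, and the phrase could mean events arising during the three months.

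The lack of an adverse-event row in Table 1 proves little. The children's blood samples, scheduled in 2.15, have no row there either. An article may also leave definitions, elicitation and causality assessment to the full protocol.

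All of this stands and limits the claim. It does not remove the point, because 2.19 states which events are collected and does not merely leave the matter out. If the temporal meaning was intended, the sentence misleads and still needs rewording.

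**Conclusion.** The point holds as a minor to moderate improvement. On its plain reading, section 2.19 makes attribution a condition for recording, with no explicitly blinded assessor named, and the staff-blinding sentences in 2.8 need reconciling. The likely effect is understated absolute risks, most plausibly in children whose underlying condition offers a ready explanation. Under the assumed 50% capture, a 10-point difference would be recorded as 5 points.

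Bias between treated and control is conditional on those attributing events knowing the arm, which the article leaves unclear. Distortion between Level 1 and Level 2 is a more direct possibility because the level is known. The actual size cannot be stated, since the document gives no event rates or capture shares. The conclusion also assumes that *associated with* is meant causally.

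**What to change.** Reword section 2.19 so that all adverse events from Day 0 to Week 12 are recorded in the same way in every arm and level, whatever the presumed cause. Ask about them at existing contacts or through the app, which already sends prompts (section 2.10). Hold relatedness as a separate field, judged without knowledge of treated/control allocation. Tabulate events by arm within level. In section 2.8, reconcile the two staff-blinding sentences by stating which staff know the level, which know the arm, and which group those handling adverse events belong to.

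The cost is a change of wording, one question at contacts that already take place, and more events to log, most of them unrelated to the intervention.

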## 3. Results

The overall objective of Stance4Health is to promote the adoption of personalised nutrition based on the use of smart mobile technologies as well as tailored food production, which will optimize GM activity. A set of new instruments developed within the project will allow for the adoption of healthy, pleasant, and sustainable dietary patterns based on the principles of the Mediterranean Diet, while also encouraging citizen engagement for an improved understanding of a healthy lifestyle. The nutritional intervention proposed here will test the efficacy of the SPN service developed by the Stance4Health project in promoting a healthy and environment-friendly lifestyle. The SPN service will be delivered to consumers through different tools such as the nutritional mobile app i-Diet Stance4Health, wearable wrist bands to measure daily activity, and production and delivery of food supplements and fortified foods for individuals or specific groups of the population (e.g., people with allergies, obesity, etc.).

To date, no studies are available that evaluated the effects of a SPN service based on the use of a nutritional app. It will allow a more personalised service to achieve better use of time, which is a benefit for the nutrition specialists and for consumers/patients.

The trial results will be important to understanding if the SNP service proposed by Stance4Health will be capable of ameliorating the intestinal microbiota and empowering consumers to make healthy and sustainable dietary choices.

## Figures and Tables

**Figure 1 foods-11-01480-f001:**
[figure not shown]
Intervention study.

**Table 1 foods-11-01480-t001:** Schedule of enrollment, interventions, and assessments for participants.

		Study Period		
	Enrollment	Allocation	Middle of the Study	End of the Study
**PROTOCOL ACTIVITY**	Day −60 to 1	Day 0	Week 6	Week 12
**TIMEPOINT**	−T1	T0	T1	T2
**ENROLLMENT:**				
Eligibility screen	X			
Informed consent	X			
Demographic details	X			
Lifestyle questionnaire		X		X
FFQ_IDEFICS/i.Family		X		X
FFQ_S4H		X		X
Bowel habits questionnaire		X		X
Allocation		X		
**INTERVENTIONS:**				
Study populations—Level 1				
Study populations—Level 2				
**ASSESMENTS:**				
Nutritional app i.Diet				
Anthropometric measurements		X		X
Stool samples		X	X	X
Urine samples		X		

The arrows represent the duration of interventions/assesment. starting at “Day 0” and finishing at “Week 12”.
